# Evaluating the effect of action-like video game play and of casual video game play on anxiety in adolescents with elevated anxiety: protocol for a multi-center, parallel group, assessor-blind, randomized controlled trial

**DOI:** 10.1186/s12888-024-05515-7

**Published:** 2024-01-19

**Keywords:** Anxiety, Adolescent, Video games, Randomized controlled trial, Digital mental health, Cognitive training, Emotion regulation, Online intervention

## Abstract

**Background:**

Adolescence is a critical period for the onset and maintenance of anxiety disorders, which raises the importance of intervening early; one possibility of doing so is via digital interventions. Within that research field, at least two important research paths have been explored in the past years. On the one hand, the anxiolytic effect of casual video games has been tested as such gaming activity may distract away from anxious thoughts through the induction of flow and redirection of attention toward the game and thus away of anxious thoughts. On the other hand, the bidirectional link between weak attentional control and higher anxiety has led to the design of interventions aiming at improving attentional control such as working memory training studies. Taking stock that another genre of gaming, action video games, improves attentional control, game-based interventions that combines cognitive training and action-like game features would seem relevant. This three-arm randomized controlled trial aims to evaluate the feasibility and the efficacy of two video game interventions to document how each may potentially alleviate adolescent anxiety-related symptoms when deployed fully on-line.

**Methods:**

The study aims to recruit 150 individuals, 12 to 14 years of age, with high levels of anxiety as reported by the parents’ online form of the Screen for Child Anxiety Related Disorders questionnaire. This trial contrasts a child-friendly, “action-like” video game designed to improve attentional control abilities in a progressive and stepwise manner (Eco-Rescue), a casual puzzle video game selected to act as a positive distraction tool (Bejeweled) and finally a control group with no assigned training intervention to control for possible test-retest effects (No-training). Participants will be assigned randomly to one of the three study arms. They will be assessed for main (anxiety) and secondary outcomes (attentional control, affective working memory) at three time points, before training (T1), one week after the 6-week training (T2) and four months after completing the training (T3).

**Discussion:**

The results will provide evidence for the feasibility and the efficacy of two online video game interventions at improving mental health and emotional well-being in adolescents with high levels of anxiety. This project will contribute unique knowledge to the field, as few studies have examined the effects of video game play in the context of digital mental health interventions for adolescents.

**Trial registration:**

The trial is registered on ClinicalTrials.gov (NCT05923944, June 20, 2023).

## Background

### Anxiety - adolescence

Anxiety is the most frequently diagnosed adolescent mental health problem in children and adolescents, with an estimated prevalence of about 7% [1, 2]. Beyond diagnosed anxiety disorders, Balász et al. [3] observed in their study that 32% of adolescents experienced subclinical levels of anxiety. Anxiety is characterized by emotion dysregulation [4, 5] and behavioural over-control [6]. Anxiety symptoms are associated with a lower general quality of life [7], worse school performance [8] and lower social functioning [9]. Moreover, adolescent anxiety tends to persist into adulthood and is related to other health problems, such as substance misuse and depression [10, 11]. Epidemiological evidence indicates that for some anxiety disorders, 50% of diagnosed adolescents show a first onset before the age of 15 [12]. Adolescence is indeed a transitional period key for structuring socialization and well-being, characterized by a limited efficacy in emotion regulation strategies and in applying attentional control in emotional contexts, as well as heightened levels of anxiety and negative mood. At the same time, adolescence is also a developmental stage highly plastic [13–15] and constitutes a sensitive window of opportunity to benefit from interventions aiming at promoting cognition and emotion regulation.

### Cognitive model of anxiety: attentional control, anxiety and emotion regulation

Emotion regulation refers to the ability to interact with emotions in a way that is consistent with personal goals [16]. Theories of emotion regulation and cognitive theories of anxiety generally agree that the capacity to cognitively regulate emotions relies on the same cognitive functions and prefrontal networks which support attentional control allowing the selection and manipulation of information (such as stimuli or thoughts) in working memory (WM) [17–24].

In the context of anxiety, individuals may have more difficulties inhibiting irrelevant information or anxious thoughts, and may therefore experience higher difficulties to prevent their access to WM. As a result, the WM capacity available for task performance is likely restricted as well as the ability to retain relevant information [25–29]. This hypothesis receives support from meta-analytical findings [29] showing the association between self-report levels of anxiety and poorer performance on measures of WM capacity (g=-0.33), in particular visuospatial WM (g=-0.41).

The underlying assumption of cognitive models of anxiety is that efficient attentional control (AC)– the ability to monitor and flexibly allocate resources to goal-relevant information while inhibiting goal-irrelevant information - is a key component for implementing cognitive emotion regulation strategies and to filter out distracting emotional stimuli or undesired thoughts. This has been backed up by evidence that interindividual differences in AC is linked to more frequent or efficient use of adaptive emotion regulation strategies, such as reappraisal [30–32], as well as neurobiological evidence that brain networks responsible for implementing emotion regulation strategies recruit regions involved in AC. In a reciprocal manner, cognitive theories of anxiety posit that anxiety impairs the efficiency of AC [24, 33], and that this in turn is likely to impact negatively individual’s ability to regulate emotions and anxiety. Previous studies have highlighted the relationship between impairments in AC skills and higher levels of anxiety in children and adolescents [34–36].

### Review of computerized cognitive trainings (CCT) and casual video game interventions

Based on the assumption that deficits in AC contribute to the etiology and maintenance of anxiety and emotion dysregulation, researchers have developed cognitive training interventions designed to train specific cognitive processes with the goal of reducing anxiety symptoms. These interventions, which have been termed computerized cognitive trainings (CCT), may offer a potentially interesting cognitive training remediation tool as well as augment treatment accessibility, since they may be performed at home and do not require the presence of a specialist.

So far, CCT interventions have often targeted the training of WM since reduced WM capacity is often identified as one of the primary cognitive deficits exhibited in individuals with anxiety [29]. Intervention studies targeting WM have commonly used the adaptive dual n-back task with the goal to increase WM resources in anxious individuals [37, 38]. Different versions of n-back training have been used, with the most well-designed ones incorporating adaptive difficulty to account for interindividual differences in executive functions and their potential for plastic changes through training. Some adaptive n-back trainings have included affective stimuli (commonly negative valence materials such as words or pictures) with the goal of reducing excessive processing of task-irrelevant affective stimuli, interfering with on-going task performance both at the perceptual level and at the executive control level. Such prioritization of affective information is proposed to be increased in individuals suffering from anxiety because of hypervigilance towards affective information. Emotional n-back training is suggested to be more prompt to induce greater reduction of anxiety symptoms by targeting affective executive control [39, 40].

A closely related field of research has developed CCT interventions with the goal to reduce the negative attentional vigilance bias that high-anxious individuals often display towards negative information, assuming that this will result in reduced anxiety. Based on the attentional control theory [24], anxiety is proposed to impair the efficient functioning of the goal-directed attentional control system, while at the same time increasing the extent to which cognitive processes are influenced by bottom-up, stimulus-driven attentional capture, particularly when stimuli carry threat-related or negative information. Anxious individuals with negative attentional vigilance bias detect and process more easily threatening stimuli, which distracts them away from task-relevant information and thus impacts the on-going task performance. Based on this theory, researchers have developed interventions - termed attention bias modification (ABM) - designed to train attention away from threatening stimuli with the expectation that this will lead to long-term reduction in vigilance to threat and in turn anxiety [41]. ABM typically uses an adaptation of the dot probe task with emotional words or faces. Unfortunately, despite earlier encouraging results, recent meta-analyses have demonstrated mixed evidence for reducing anxiety symptoms [42–45]. Findings from these meta-analyses highlighted that attention bias in anxiety is multifaceted and more dynamic than just a hypervigilance towards threat. As such, attention bias modification programs that simply train attention away from threat may too narrowly target one specific attentional vigilance mechanism that contributes to anxiety.

In the past years, there has also been growing interests in using video games for delivering interventions to help adolescents to learn to better regulate their emotions using non-stigmatizing games that have the potential to increase adherence to treatment [46–48]. A line of research within that field, interested in the impact of videogames on emotions, has documented the short-term beneficial effects of playing casual or puzzle videogames on stress, anxiety and mood [49–52]. Casual video games are video games targeted for a large audience, which are fun, fast to access, and simple to learn. They are also efficient at restricting attention to the game, possibly via the induction of Flow, acting as a powerful distraction from anxious thoughts and daily stress. In several interventions, Russoniello and colleagues have shown that participants assigned to play a casual game of their choice three times per week, for 30 min, over a 1-month period, showed substantial reduction in stress, anxiety and depression [49–52]. While these interesting effects on anxiety were assessed shortly after the intervention, whether their impact on emotion regulation and anxiety may be longer-lasting remains understudied.

### The multiple object tracking (MOT) paradigm and dual tasking

To better address the variety of attentional and regulation issues noted in anxious individuals, both at the bottom-up level and at the top-down level, we aimed at designing a training intervention that encourages the coordinated use of multiple attentional control functions at the same time– rather than focusing on a single attentional function. The Multiple Object Tracking (MOT) task is a paradigm that not only adequately reflects the demands of complex and dynamic human environments but also gathers several aspects of attentional control functions, including sustained and distributed attention as well as visuo-spatial working memory [53]. The MOT task consists of focusing attention on a limited number of moving targets appearing among moving distractors. After selective attention is applied to select a target set, sustained attention to the moving targets is in high demand as moving targets become indistinguishable from moving distractors. Such tracking requires both sustained and distributed attention as task-relevant stimuli move across the screen among other, as similarly looking distractors. Attentional demands vary depending on the number of targets to track, the speed of moving targets, as well as the distance between targets and distractors as tracking proceeds. In sum, tracking objects in a dynamic scene requires a demanding maintenance and updating of object information in working memory as well as sustained attention to the location of the to-be-tracked items [54, 55].

In the context of CCT, the MOT paradigm has been used to train cognitive functions with different populations (i.e. athletes, military, patients with neurodevelopmental disorders) and encouraging results have been reported. For example, Tullo [56] used a 3D MOT to train attentional abilities in adolescents (11–15 years old, *N* = 129) with neurodevelopmental disorders (i.e. autism spectrum disorder; attention deficit hyperactivity disorder, intellectual disability). Significant improvement of attention was observed in the MOT training group compared to both the distraction group (who played the game *2048)* or the passive no-training group. Harris et al. [57] did an intervention with 84 students randomized to a MOT training group or a passive no-training group. They showed that MOT training improved WM performance compared to the control condition. Vartanian et al. [58] conducted an intervention (*N* = 41 members of the Canadian Armed Forces) with MOT training that also showed improvements in WM performance in the training group compared to a passive no-training control group. Nyquist et al. [59] also used MOT training with low vision children and reported greater enhancement of their peripheral vision compared to a control video game training (*Tetris*), with improvements still noted 12 months after training.

To our knowledge, training attentional control skills through the MOT training regimen has never been investigated in anxious adolescents. Based on the link between impairments in attentional control abilities and anxiety highlighted in the literature, the MOT paradigm appears as a promising training regimen to target attentional control, and possibly reduce anxiety. We designed a training intervention based on the MOT paradigm described below and made it all the more demanding on attentional control by adding a visual detection task that automatically summon attention to the to-be-detected item. Such dual-task demands during training are known to facilitate attentional enhancement [60].

### Gamified training

Another feature of the proposed intervention is the inclusion of the MOT-detection dual task in a gamified environment. It has been proposed that intervention strategies which use gamification and computerized games have the potential to increase the adherence and impact of cognitive interventions [61]. We expect the implementation of game elements in the MOT-dual task training to be specifically suited for anxious adolescents for several reasons. Within this age range, there is a need for developing new digital interventions to support mental health and well-being. Video games are immersive and motivate a wide range of behaviors in adolescents, with 79% of Swiss youth playing video games every day on average one hour during the week and two hours during the weekend [62]. Similarly, 70.2% of Israeli teenagers play video games at least four times a week and spend on average two hours daily on this activity [63, 64]. As such, video games (both serious and entertainment video games) represent one of the most appealing digital interventions for addressing the issues of accessibility and engagement frequently encountered in mental health interventions [48, 65]. Video game elements can make this training intervention more enjoyable for adolescents, through the use of a familiar medium that feels safe, gratifying and immersive, thus helping adolescents to better maintain their motivation during an extensive training schedule [66].

In the context of mental health, a growing body of findings highlight the benefits (i.e., cognitive, motivational, and emotional) video games may confer upon users [48, 67–71]. For instance, by prescribing commercialized casual video games to adults, with the instruction to play three times per week, each session lasting thirty minutes, over a one-month period, a few randomized studies have established a causal reduction in stress, depression and anxiety [49, 51]. Scholten et al. [72] investigated the efficacy of a biofeedback video game for adolescents with high levels of anxiety compared to a distraction video game (*Rayman 2*: *The Great Escape*) and both conditions showed reduction in anxiety, which is promising for upcoming interventions studying video game effects on mental health.

### Study objectives

The aim of this three-arm randomized controlled trial is to evaluate the feasibility of a 6-week video game training intervention to reduce adolescent anxiety-related symptoms. This study will also provide a first window into the efficacy of the proposed treatments when entirely deployed on-line in a young adolescent sample. The first group of participants will receive *Eco-Rescue*, an action game-based intervention (i.e. dual-task training) designed to train attention control. A second group will receive *Bejeweled 3*, a commercialized casual video game (i.e. puzzle game) that does not specifically target attentional control but has shown to reduce anxiety in previous studies, arguably through providing a distraction away from anxious thoughts [49]. A third, no-training control group will not receive any training, providing a needed control for any test-retest effects and allowing us to assess the extent to which the two video game genres proposed may impact self-report and behavioral outcomes (see Fig. 1 for study flowchart).

### Trial design and hypotheses

This randomized controlled trial study uses a multi-center, assessor-blind, superiority trial with three parallel group (3 groups × 3 time points) with primary and secondary endpoints assessed at baseline (T1), one week after completing the 6-week intervention or no-training period (T2) and 4 months after completing the assigned intervention (T3). We will investigate the following hypotheses:

#### Primary endpoint

*Video Game Intervention Hypothesis*. Anxiety may be reduced in adolescents through video game play because of their beneficial effects on attentional enhancement and/or the distraction away from anxious thoughts such play activity may trigger. We expect a significant effect on reducing anxiety symptoms from baseline (T1) to post-assessment (T2) for the two intervention groups (*Eco-Rescue*, *Bejeweled*) compared to the control group (*No-training*). Anxiety will be assessed with the Child Version of the self-report questionnaire of the Screen for Child Anxiety Related Emotional Disorders (SCARED-C).

#### Secondary endpoints

*Attentional Control Hypothesis*. Attentional control may be improved with an action game-based intervention. We expect the Eco-Rescue intervention to significantly increase attentional control from baseline (T1) to post-assessment (T2) compared to the No-training group and possibly Bejeweled, as measured by computerized tasks including the Useful Field of View (UFOV) and the Test of Variables of Attention (TOVA).

*Affective Control Hypothesis*. Affective control (i.e. attentional control applied in the presence of emotional distractors) can be improved with an action game-based intervention. We expect an increase in affective control for the Eco-Rescue game training group from baseline (T1) to post-assessment (T2) compared to the No-training one and possibly Bejeweled, as measured by the Affective Backward Digit Span (ABDS) task.

#### Exploratory endpoints

*Near-Transfer.* We expect the Eco-Rescue intervention to significantly increase performance on the MOT task from baseline (T1) to post-assessment (T2) compared to the No-training and the Bejeweled groups.

*Relationship between Attentional Control and Anxiety*. We expect greater attentional control to be associated with lower anxiety-related symptoms at baseline-assessment. If confirmed, we will then investigate the extent to which attentional control improvements (as measured by the UFOV and TOVA) may be associated with greater diminution in anxiety scores (SCARED Child version).

*Relationship between Attentional Control and Mental Health outcomes*. As the literature highlights a link between attentional control and mental health outcomes, we will also investigate whether greater attentional control (as measured by the UFOV and TOVA) is associated with greater affective control and emotion regulation abilities, and fewer self-reported mental health problems (e.g. depression). Affective control will be assessed using the Affective Backward Digit Span (ABDS) task while emotion regulation abilities will be assessed using the Cognitive Emotion Regulation Questionnaire and depression by the Patient Health Questionnaire (PHQ- 8).

*Relationship between Attentional Control and* in-game learning. We will evaluate whether better progression in the Eco-Rescue game may be related to higher attentional control (as measured by the UFOV and TOVA).

*Relationship between computerized tasks and self-report measures.* We will ask how task-based assessments relate to self-report measures for (i) attentional control (UFOV and TOVA versus Attentional Control Scale) and for (ii) emotional control (ABDS versus Cognitive Emotion Regulation Questionnaire).

*Motivation.* We will look at the impact of motivation to play the game (as measured by the Intrinsic Motivation Inventory) on intervention outcomes contrasting the Eco-Rescue and the Bejeweled groups.

*Expectation*. We will look at expectation about the intervention effects (based on the Expectation Questionnaire) contrasting the Eco-Rescue and the Bejeweled groups.

*Durability of effects*. We will explore long-term changes in intervention outcomes between baseline (T1) and follow-up (T3).

## Methods

### Study setting

This study will be completed both online and in the laboratory; more precisely, all game-related training will occur on-line, from the comfort of participants’ home, whereas all pre, post and follow-up assessments will be carried out in the laboratory. The study will be carried in parallel at two different sites: the [name] lab at the University of Geneva in Switzerland and the [name] lab at the University of Haifa in Israel.

### Eligibility criteria

Eligible adolescents are those aged 12 to 14 years old, who own or have access to a computer, have access to the Internet, have an active mobile phone number, and score at 17 or higher on the parent version of the Screen for Child Anxiety Related Disorders (SCARED-P). Participants will be ineligible if they have a history of neurological injury (i.e. head injury), a diagnosed neurological or neurodevelopmental disorder (i.e. autism spectrum disorder), a diagnosed intellectual disability, a diagnosed psychosis or bipolar disorder or if they are currently enrolled in another cognitive training intervention. Uptake of other anxiety interventions during the study is permitted and will be assessed at screening, post and follow-up.

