### Participants recruitment

150 adolescents will be recruited through flyers, advertisements on the lab website, mental health adolescent units, and social media platforms advertising the study in Geneva and Haifa. Study adverts will direct interested participants and their families to a Qualtrics page. There, they can review the study information, may choose to undertake screening and provide consent to be signed by the parent or legal guardian using the provided links. Regarding the recruitment site in Geneva, participants will be provided with contact information for local mental health and crisis support services in the information form to provide adequate information in case participants require care and support. Direct contact between the participant and the study team will not be required during recruitment and study enrolment. After signing the consent form, families will be redirected to online questionnaires to screen participants’ suitability for inclusion. Eligible participants will be redirected to a short contact form to collect their name, phone number and email address to be contacted by the research team and set up an appointment at the University of Geneva (Switzerland) or at the University of Haifa (Israel). Personal information will be stored in our secure system on university servers. Adolescents recruited will be provided with adapted study information and will sign an assent form before starting the baseline assessment. This study has been approved by the Ethics Board of the University of Geneva (CUREG) and by the Institutional Review Board (IRB) of the University of Haifa.

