### Randomization and allocation

The study will have two training arms and one passive arm. After completing baseline assessment, participants will be randomized to one of the three following arms: the attentional control - Eco-Rescue intervention, the distraction - Bejeweled intervention or the No-training control group. Arm allocation will be concealed to the blinded experimental staff by using computer-generated condition assignment stratified by sex and anxiety score at baseline (assessed by the SCARED-C). To this end we will use the algo detailed in Sella et al. [75]. Such a procedure retains the value of a fully randomly assigned design, while simultaneously minimizing between group variance on the to be matched variables. Randomization will be performed separately for each site. Experimenters blinded to arm allocation will conduct assessments at each timepoint (baseline, post- and follow-up). The experimenters unblinded to the arm allocations will be responsible for administering the general instructions and technical support at any stage of the study and will take care of monitoring participants during the six weeks intervention period. Statistical analyses will be conducted by researchers blind to arm allocation.

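### Other anxiety treatment is recorded before randomisation but used in neither the stated allocation nor the stated primary model, at some cost in precision; whether cognitive training may begin after randomisation is also unclear

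*Protocol article*

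**What the plan says.** All references are to the protocol article.

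- **Eligibility criteria.** On concomitant treatment: "Uptake of other anxiety interventions during the study is permitted and will be assessed at screening, post and follow-up". The one exclusion that concerns a current intervention applies to adolescents "if they are currently enrolled in another cognitive training intervention". No criterion excludes adolescents already receiving anxiety treatment. That they are eligible is an inference, but asking at screening makes little sense otherwise.
- **Participants recruitment.** "150 adolescents will be recruited through flyers, advertisements on the lab website, mental health adolescent units, and social media platforms" are the channels, so some entrants will probably already be in care.
- **Participant timeline.** Screening precedes the baseline assessment, and randomisation follows baseline. The screening answer is therefore a true pre-randomisation variable.
- **Randomization and allocation.** Arms are assigned by "computer-generated condition assignment stratified by sex and anxiety score at baseline (assessed by the SCARED-C"), and "Randomization will be performed separately for each site". No other factor is named.
- **Data analysis.** The mixed model has fixed effects of time, group and group by time, random intercepts for subject and site, and a random slope of time. Hypotheses are tested by 2 × 2 repeated-measures ANOVAs with no covariate named.
- **Background, review of computerised cognitive trainings.** Here "researchers have developed cognitive training interventions designed to train specific cognitive processes with the goal of reducing anxiety symptoms".

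**The concern.** The primary endpoint is change in SCARED-C from T1 to T2. Two adolescents with the same T1 score, one in treatment and one not, may follow different courses over the training period. Balancing on the T1 score does not balance the expected course. If treatment status predicts change, leaving it out of the model leaves explainable variance in the residual and makes the arm contrasts less precise than the collected data allow. The sample is small (38 per arm planned for the final sample), so a free gain in precision is worth having.

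The second matter is wording. Cognitive training is an exclusion at entry, other anxiety interventions may be taken up later, and the Background presents cognitive training as a means of reducing anxiety. A reader applying the rules to a No-training participant who begins such a programme after randomisation cannot tell how the protocol classes it.

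**Working it through.** **The plan's own figure.** The Sample size section gives 38 per group for the 2 × 2 design, from g = 0.25 in absolute value, correlation 0.70, alpha 0.05 and power 0.80. With f = 0.25/2 = 0.125 and N = 76, the noncentrality is 0.125² × 76 × 2 / (1 − 0.70) = 7.92. Power is 79.3% at 38 per group and 80.4% at 39, so the figure reproduces within tolerance. The point does not rest on it; only the correlation of 0.70 is carried forward.

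**Inputs for the size of the effect**
- Change-score variance in units of baseline SD², with equal variances at T1 and T2: 2 × (1 − 0.70) = 0.6 (correlation from the Sample size section).
- n = 50 per arm as recruited (Sample size section).
- p, the proportion treated at entry: assumed 0.15 to 0.30. Not in the documents.
- d, the extra T1–T2 change in treated adolescents: assumed 0.3 to 0.8 SD. Not in the documents.

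**Standard error of a pairwise contrast without adjustment.** √(2 × 0.6/50) = 0.155 SD; 95% half-width 1.96 × 0.155 = 0.30 SD.

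**Share of change variance due to status,** p(1 − p)d²/0.6, **and relative fall in the standard error,** 1 − √(1 − share):

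| p | d | share | fall in SE |
|---|---|---|---|
| 0.15 | 0.3 | 0.1275 × 0.09 / 0.6 = 0.019 | 1.0% |
| 0.20 | 0.5 | 0.16 × 0.25 / 0.6 = 0.067 | 3.4% |
| 0.30 | 0.8 | 0.21 × 0.64 / 0.6 = 0.224 | 11.9% |
| any | 0 | 0 | 0 |

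**Is chance imbalance an extra error?** The standard error of the between-arm difference in proportion treated is √(2p(1 − p)/50): 0.071 at p = 0.15 and 0.092 at p = 0.30. Multiplied by d, it adds a standard deviation of 0.0214 SD (low case) or 0.0733 SD (high case) to the contrast. Squared, and divided by the contrast's variance of 0.024, these give 0.000459/0.024 = 0.019 and 0.00538/0.024 = 0.224. These are the variance shares in the table. The imbalance is thus a component of the 0.155 SD standard error and not an addition to it.

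**Which model term helps.** With two time points, a main effect of status shifts a participant's T1 and T2 alike and cancels from the change. Only a status-by-time term, or status as a covariate in a model for T2 given T1, acts on the group-by-time contrast.

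**The eligibility wording.** The exclusion is phrased in the present tense, for entry. The permission covers the study period and does not define other anxiety interventions. The Background passage supports including cognitive training in that term. The fact that the eligibility text names cognitive training separately, just before, supports excluding it. Nothing in the article decides between the two.

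**The case against.** Four objections have force.

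- **Randomisation already handles imbalance.** This stands. A reader might infer that unbalanced treatment status biases the comparison, and might set a 1.96-SE imbalance (a shift of 0.04 to 0.14 SD) against the planning value of 0.25, which gives 17–58%. The documents do not support that reading. The shift is a tail value of ordinary sampling error, is centred on zero and is already covered by the confidence interval.
- **The gain is assumed.** This also stands. The documents say neither how many adolescents will be treated nor how their course differs. Those in long-standing care may not change differently at all, and the 12% needs both upper assumptions at once.
- **An unseen analysis plan may hold the adjustment.** This stands in part. Uptake tables by arm and sensitivity analyses are commonly left to that plan and are not counted as missing here. The article does, however, name its allocation factors and list its model terms, and this item is in neither list.
- **There is no contradiction in the eligibility text.** This stands. A reader might infer that the two sentences conflict, or that controls are allowed to start cognitive training. One sentence is an entry criterion and the other a rule for the study period, and such rules may properly differ. The article does not say that cognitive training may begin after randomisation. What remains is an ambiguity.

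Permitting and recording other care also fits an intention-to-treat comparison in which controls carry on as normal. The point does not question that choice.

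**Conclusion.** The point holds as a modest matter of precision. A plausible predictor of change, collected before randomisation at no extra cost, is absent from the stated allocation and primary model. Using it would reduce the standard error of the T1–T2 contrast by about 1–12% under the assumed ranges, about 3% at the middle values tried, and not at all if status is unrelated to change. These figures depend on the assumed p and d and on the change variance of 0.6 SD² derived from the planned correlation. Validity is not threatened: the unadjusted comparison remains unbiased in expectation with respect to treatment at entry.

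The wording on cognitive training is a separate and smaller matter of clarity. How often a participant would start such training cannot be judged from the article.

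**What to change.** 1. Prespecify receipt of an anxiety intervention at screening (yes/no) in the primary SCARED-C analysis, as a status-by-time term in the repeated-measures model or as a baseline covariate in an ANCOVA on T2. A main effect alone will not do. The cost is one degree of freedom for the status-by-time term or the ANCOVA covariate; no new data are needed.
2. Optionally, add the same item as a balancing factor within site. Enrolment was expected from January 2024, so this applies only if the allocation script can still be changed. The cost is slightly looser balance on sex and SCARED-C. The model term is worthwhile without it.
3. Reconcile the two eligibility sentences so that it is clear whether cognitive training begun after randomisation counts as a permitted other intervention. Which rule applies is for the trial team; none is proposed here. The cost is one clarified sentence.

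A screening covariate does not address uptake that differs by arm after randomisation. That belongs with the uptake data at T2 and T3, for which the analysis plan may already provide.
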